### Objectives

It is the objective of the quantitative component of this study to

1. explore whether facilitation of clinical reasoning skills via a clinical mentoring programme delivered to clusters of physiotherapists (outpatient musculoskeletal physiotherapy departments) yields greater improvements in patient outcomes (measured by risk-adjusted patient outcomes measures from clusters of patients at each step) than those yielded with usual training
2. explore whether facilitation of clinical reasoning skills via a clinical mentoring programme relates to improved physiotherapist performance in clinical reasoning, and whether changes in performance correlate with improvements in patient outcomes

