### Hypotheses

H: There will be a significant difference in the risk-adjusted outcomes of patients whose physiotherapists have received training in clinical reasoning skills via a clinical mentoring programme when compared with those whose physiotherapists have received standard training.

H: There will be no difference in the risk-adjusted outcomes of patients whose physiotherapists have received training in clinical reasoning skills via a clinical mentoring programme and those whose physiotherapists have received standard training.

H: There will be a significant improvement in the performance of physiotherapists who have received training in clinical reasoning skills via a clinical mentoring programme when compared with their performance having received standard training.

H: There will be no improvement in the performance of physiotherapists who have received training in clinical reasoning skills via a clinical mentoring programme when compared with their performance having received standard training.

H: There will be a correlation between improvements in the performance of physiotherapists who have received training in clinical reasoning skills via a clinical mentoring programme and improvements in the clinical outcomes of their patients.

H: There will be no correlation between improvements in the performance of physiotherapists who have received training in clinical reasoning skills via a clinical mentoring programme and improvements in the clinical outcomes of their patients.

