#### **Analysis**

The PAM score will be calculated using the standard scoring table, and patients will be classified into one of the four levels of activation outlined in the validity studies for the tool.

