### Procedures

It is the *differences* in patient outcomes data that is being measured. Outcomes data will be collected from a cluster of patients being treated by each participating therapist at each stage of the stepped wedge design, giving 4 clusters of patient data per physiotherapist cluster for within group and between group comparison.

For each patient, outcome data will be collected at first and last appointment and at 12 months post discharge. The long term follow up is important in that – as Resnik (Resnik, 2007) points out - it is possible that aspects of physiotherapy intervention (for example, patient education) have health effects which are lifelong and therefore cannot be measured purely with discharge measurements of the patient's status. All patients treated sequentially by the therapist will complete the outcomes until a full data set is obtained.

Patient data loss from failure to complete treatment / DNA will be minimized by telephone contact, having consented patients to being contacted by the researchers by telephone as part of the study follow up. Patients refusing to complete data or withdrawing consent will be reported as will the reasons for failure to complete treatment and / or outcomes.

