### Strategies to Enhance Quality of Outcomes

#### Risk Adjustment

To enhance the quality of these outcomes, control of variables that could affect the dependent variables (patient outcomes) is essential before comparing patient outcomes are compared between clusters and within clusters. While no consensus exists for the optimal risk-adjustment method, an approach to risk adjustment has been previously used for outcomes research in physiotherapy (Jette and Jette, 1996; Resnik and Hart, 2003). First, using data from step 1 (before any therapists have commenced intervention) univariate analyses will be used to identify possible confounding variables among patient characteristics (from previous literature, age, severity, sex, onset of condition, number of surgeries for condition, reimbursement, exercise history and employment status).

Next, a general linear model (GLM) will be developed for the HRQL outcome measures—the PSFS and EQ-5D. Each patient characteristic found to be significant in the univariate analyses will be included in the models using a backward-deletion process. General linear models allow for simultaneous control of continuous and categorical variables in the risk-adjustment process. It is the risk-adjusted HRQL data that will be used for all data analysis to analyse the effect of the intervention.

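### Risk adjustment is specified only for PSFS and EQ-5D, although the objective and hypothesis promise risk-adjusted patient outcomes, which also include PAM and MRPS

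*Protocol*

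**What the plan says.** The protocol sets a general principle, and then a model that covers only part of it.

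- **Principle.** Under Risk Adjustment, "control of variables that could affect the dependent variables (patient outcomes) is essential before comparing patient outcomes".
- **Objective and hypothesis.** The first quantitative objective is about improvement "measured by risk-adjusted patient outcomes measures from clusters of patients at each step". The first hypothesis reads "There will be a significant difference in the risk-adjusted outcomes of patients whose physiotherapists have received training". Neither is limited to health-related quality of life.
- **Outcomes in scope.** Table 1 lists four instruments under patient outcome: PSFS, EQ-5D, MRPS and PAM.
- **Model.** Risk Adjustment then says "a general linear model (GLM) will be developed for the HRQL outcome measures", which it names as the PSFS and EQ-5D, and adds: "It is the risk-adjusted HRQL data that will be used for all data analysis to analyse the effect of the intervention".
- **PAM and MRPS.** Their Analysis paragraphs deal with scoring only. For activation, "The PAM score will be calculated using the standard scoring table" and patients are placed in four levels. For satisfaction, the instrument authors' scoring database is used.
- **Form of the outcome.** Procedures says that differences in patient outcomes are what is measured. Table 5 has columns for PAM and MedRisk differences.
- **Comparison model.** Statistical methods describes an ANOVA with a random intercept. The section on challenges of the design adds time effects. Neither names a patient covariate.

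**The concern.** In this design the physiotherapist can serve as his or her own control, but the patients cannot. Procedures states that "Outcomes data will be collected from a cluster of patients being treated by each participating therapist at each stage of the stepped wedge design", so control and mentored periods contain different people. Under Randomisation (Enrollment), patients are recruited and consented by their own physiotherapist. Under Blinding, the physiotherapists know when they receive the intervention. Periods last 12 months. Randomising the order of three clusters does not ensure that case-mix is balanced between conditions, and the protocol's own risk-adjustment principle answers exactly this problem.

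Followed as written, that principle reaches two of the four patient outcomes. Any PAM or MRPS comparison between control and mentored periods would carry case-mix differences into the estimate. PAM would also lose some precision, because it is measured at the first appointment (the activation items are in the appended baseline questionnaire) and that value is not used as a covariate.

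**Working it through.** **1. The protocol's own power figure.** This is the only power result in the document and it concerns the PSFS. Inputs from Sample size and Appendix E: I = 12, T = 4, N = 9, σ² = 4/9 = 0.4444, τ² = 1, θ = 1, U = 24, W = 224, V = 56.

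Var = Iσ²(σ² + Tτ²) / [(IU − W)σ² + (U² + ITU − TW − IV)τ²]

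= 12 × 0.4444 × 4.4444 / (64 × 0.4444 + 160) = 23.704 / 188.444 = 0.125786.

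SD = 0.354663, θ/SD = 2.8196, power = 0.805, total 4 × 12 × 9 = 432. All agree with the protocol, and nothing in this point changes them.

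**2. Scope of adjustment, outcome by outcome.**

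| Outcome | Patient outcome in Table 1 | Within objective and hypothesis | Adjustment model given |
|---|---|---|---|
| PSFS (primary) | yes | yes | yes |
| EQ-5D | yes | yes | yes |
| PAM | yes | yes | none |
| MRPS | yes | yes | none |

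**3. Precision for PAM.** The protocol gives no PAM standard deviation, effect size or first-to-last correlation, so the correlation ρ is assumed. With equal variance at both appointments, and relative to the variance of a single score:

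- change score: 2(1 − ρ)
- last score adjusted for first score: 1 − ρ²
- ratio, adjusted to change: (1 + ρ)/2

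| ρ (assumed) | Change | Adjusted | Ratio | Cut in residual variance |
|---|---|---|---|---|
| 0.3 | 1.40 | 0.91 | 0.65 | 35% |
| 0.5 | 1.00 | 0.75 | 0.75 | 25% |
| 0.7 | 0.60 | 0.51 | 0.85 | 15% |

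**4. Does physiotherapist-level variance change this?** As a rough check, borrow the PSFS base case in step 1, hold τ² = 1 and multiply σ² by each ratio.

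- 0.65: σ² = 0.2889; Var = 12 × 0.2889 × 4.2889 / (64 × 0.2889 + 160) = 14.868 / 178.489 = 0.0833, which is 34% below 0.1258.
- 0.75: σ² = 0.3333; Var = 17.333 / 181.333 = 0.0956, 24% below.
- 0.85: σ² = 0.3778; Var = 19.846 / 184.178 = 0.1078, 14% below.

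The variance of the estimated effect falls almost in step with the residual variance. The ratio of the two variance components for PAM is unknown, so this is only an illustration.

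**5. Bias from imbalance in baseline PAM.** If mean first-appointment PAM differs by d SD between control and mentored patients, a change score is biased by (1 − ρ)d in size. For an assumed d = 0.2 this is 0.14, 0.10 and 0.06 SD at ρ = 0.3, 0.5 and 0.7. No such imbalance is shown in the document. For MRPS no figure can be given.

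**The case against.** The strongest reply is that the protocol never states how PAM or MRPS will be compared. Their paragraphs give scoring only, and covariates for secondary outcomes are commonly left to a SAP, which is not at hand. Table 5 is a per-physiotherapist display for the mixed-methods work, not an analysis model. Its satisfaction column may mean before versus after mentoring, since the satisfaction items ask about treatment already received. This stands as a limit: the unadjusted first-to-last comparison is an inference from Procedures, Statistical methods and Table 5. It does not remove the mismatch, because the protocol is not silent on scope. It names the outcomes to be modelled, and the list is narrower than its own objective.

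Second, other text points towards wider adjustment. The Table 1 row on demographic data seems to have lost a word between primary and outcomes, probably secondary. The Variables section lists patient age, condition and prognostic barriers as control variables for the dependent variables in general. The ÖMPQ is to be cross-referenced with the other outcomes. None of these supplies a method, and cross-referencing is not adjustment. They suggest that a wider scope was intended, so they add to the inconsistency.

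Third, read literally, the sentence on risk-adjusted HRQL data may mean that only PSFS and EQ-5D serve to estimate the intervention effect. No biased PAM or MRPS effect would then be reported. But the objective and hypothesis would then promise more than the analysis delivers, and would still need narrowing.

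Fourth, a first-to-last difference already subtracts the baseline. That is correct. What is missing is regression adjustment for it. Regression to the mean biases the comparison only if baseline PAM differs between conditions.

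**Conclusion.** The point holds as a minor one. The protocol limits its adjustment model to PSFS and EQ-5D while its stated principle, first objective and first hypothesis cover patient outcomes generally. Two secondary outcomes, PAM and MRPS, are left without patient covariates in a design where each step brings new patients recruited by physiotherapists who are not blinded. The possible gain in precision for PAM is 15% to 35% of residual variance. It rests on assumed correlations of 0.7 to 0.3 and on equal variance at both appointments.

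A reader might infer more than the document supports:

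- That it prescribes an unadjusted PAM change score. It does not; that is inferred.
- That baseline PAM is ignored altogether. A change score subtracts it.
- That PAM would lose a known amount of power. An effect with 80% power on the change score would have about 94%, 90% or 86% after adjustment at ρ = 0.3, 0.5 or 0.7, but both the 80% start and the correlations are assumed.
- That the main result is at risk. The PSFS is adjusted, and no figure in the protocol changes.

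**What to change.** In Risk Adjustment, extend the patient-level adjustment to all four patient outcomes:

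- **PAM:** analyse the last-appointment score in the stepped-wedge model, with first-appointment PAM and the baseline case-mix covariates collected for the PSFS model. The four activation levels can stay as a descriptive summary.
- **MRPS:** analyse the last-appointment score in the same model with the case-mix covariates only.
- **Table 1:** correct the row on demographic data so that it says which outcomes are risk-adjusted.

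If the sponsor does not want this, restrict the first objective and first hypothesis to PSFS and EQ-5D, and label PAM and MRPS comparisons as unadjusted.

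The cost is a few sentences and slightly more analysis work. No further data are needed beyond what the PSFS model itself requires. Number of surgeries and exercise history are named as candidate covariates but are not visible in the questionnaire pages at hand, so it cannot be confirmed that every candidate is on the baseline form. Covariates chosen for the PSFS may also predict activation or satisfaction less well, which limits the gain but does not argue against including them.

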#### Psychosocial Screening

In addition to risk adjustment, a formal assessment of levels of psychological distress and / or depression of patients will be made due to the fact that it is now widely accepted that such factors are strong predictors of outcome in musculoskeletal conditions (Main et al., 2007) and that pain is best viewed as a multi-dimensional phenomenon, comprising biological, psychological, social and existential elements (Westman et al., 2008). For the individual patient, persistent musculoskeletal pain has been shown to significantly affect the patient's quality of life with symptoms usually being continuous and disrupting a variety of functions (Costa Lda et al., 2011, Heymans et al., 2010, Lin et al., 2011). However, it must be remembered that not all

patients develop chronic problems – for example it has been shown that after an acute bout of back pain, only a small percentage (3–10%) of patients developed long-term work absence but this small number consumed approximately 75–85% of the available resources (Reid et al., 1997, Nachemson et al., 2000, Friedly et al., 2010). The Örebro Musculoskeletal Pain Questionnaire (ÖMPQ) will be used for this formal assessment on the basis of its predictive ability to identify patients who will have a poor outcome across a range of musculo-skeletal conditions – acute, subacute or chronic, and different body regions; any improvements (or lack of improvements) in the other outcome measures need to be cross-referenced with these profiles. (Brown, 2008, Dunstan et al., 2005, Gabel et al., 2010, Hockings et al., 2008, Johnston, 2009, Linton and Boersma, 2003, Maher and Grotle, 2009, Margison and French, 2007, Westman et al., 2008).

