| Patient distress and anxiety                                                                                        | To cross reference and enhance primary and secondary outcomes                                                                                                     | Örebro Musculoskeletal Pain Questionnaire (ÖMPQ)                                                | 1. Predictive ability to identify patients who will have a poor outcome across acute, sub-acute or chronic musculo-skeletal conditions.
2. Predictive ability to identify patients who will have a poor outcome across different body regions.                                                                                                                                                             |
| Patient demographic and healthcare utilisation data                                                                 | To enable adequate risk adjustment of primary and outcomes and cost effectiveness analysis                                                                        | Questionnaire                                                                                   | Items previously shown in other studies to be useful for risk adjustment and cost effectiveness are included.                                                                                                                                                                                                                                                                                                 |
| Therapist Performance                                                                                               | Previous educational research has measured performance; assessment will allow for triangulation of patient outcomes data with that of therapist performance.      | University course M level descriptors for assessing therapist performance on clinical placement | 1. Accepted and established form of assessing performance on M level courses where clinical placements are used.
2. Supporting research for the construct.                                                                                                                                                                                                                                                 |

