## Sample size

The primary outcome measure, the PSFS, shows that for any individual patient, the minimal detectable change (90%CI) for an aggregate of 3 or more activities is 2 points; the minimum detectable change (90%CI) for a single activity is 3 points. In this study, we are looking for a mean difference of 1 point greater improvement in PSFS scores of patients whose physiotherapists who have received the intervention compared with the PSFS scores of patients whose physiotherapists have not yet received the training, as well as a greater proportion of patients achieving the level of minimal detectable difference. The following data values were used for the power calculation: mean changes on the PSFS from usual training to the new training of 1 point, and a Standard Deviation within each group of 2. The standard deviation was on the basis of PSFS data collected from an audit of 191 patients who had received treatment at the University Health

Board physiotherapy department, which is a slightly more conservative estimate than standard deviation values of PSFS outcomes from published studies (Hefford et al., 2009, Young et al., 2010, Costa et al., 2009).

A paper published on the design and analysis of stepped wedge designs (Hussey and Hughes, 2007) investigated the statistical characteristics of the stepped wedge design for CRCTs, and through the use of theoretical calculations and simulation the authors outline a procedure for computing power in stepped wedge trials. Using this procedure, a power calculation was carried out by [name], Senior Lecturer in Statistics, Swansea University in discussion with the rest of the research team. The power calculation is summarised below:

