### **Power calculation: summary**

Following the notation of Hussey & Hughes (Hussey and Hughes, 2007), and defining

- I to be the number of physios (the maximum available would be 18; assuming recruitment of two-thirds of the maximum to be a realistic prospect, so we are primarily interested in  $I = 12$ )
- T to be the number of time points (4 time points are required to allow baseline measures and for 3 clusters to cross over from control to intervention, so we are primarily interested in  $T = 4$ )
- N to be the number of observations per physiotherapist per time point.

The model is

$$Y_{ijk} = \mu + \alpha_i + \beta_j + \theta X_{ij} + \varepsilon_{ijk}$$

where  $Y_{ijk}$  is the  $k^{th}$  observation at time  $j$  for physiotherapist  $i$ , and we assume that there is a random physiotherapist effect, so

$$\alpha_i \sim N(0, \tau^2)$$

and some random variation across observations, so

$$\varepsilon_{ijk} \sim N(0, \sigma_\varepsilon^2)$$

with independence everywhere. The  $X_{ij}$  are indicator variates, with value 0 before the intervention, and the value 1 thereafter. The range of indices are  $i = 1, \dots, I; j = 1, \dots, T$  and  $k = 1, \dots, N$ . We take  $\beta_T = 0$  in order to avoid identifiability problems, and wish to consider  $\vartheta$ , the difference in means in the control and intervention group. The variance of  $\hat{\vartheta}$  is given in equation (8) in Hussey & Hughes (Hussey and Hughes, 2007), and its calculation requires the specification of  $\sigma_\varepsilon^2$  and  $\tau^2$ , with  $N$  appearing through

$$\sigma^2 = \frac{\sigma_\varepsilon^2}{N}$$

Omitting some algebra, statistical power, based on the usual 95% confidence level, is defined by

$$1 + \Phi(-1.96 - \Delta) - \Phi(1.96 - \Delta)$$

where

$$\Delta = \frac{\theta_A}{\text{Var } \hat{\theta}}$$

and  $\Phi(\bullet)$  is the usual cumulative distribution function for the standard Normal distribution, and is implemented in EXCEL as =NORMSDISTO.

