#### Base case details

- Here, we take  $\theta = 1$  (that is, assume that the average effect of the intervention is 1), and (based on calculations on previous data) set  $\sigma_\varepsilon = 2$ . The remaining calculations are laid out in the attached spreadsheet, where, for illustration, if we take  $N = 9, \tau = 1$  then

$$Var(\hat{\theta}) = 0.12576 \dots,$$

and

$$\Delta = 2.819574$$

so that the power is

$$1 + \Phi(-1.96 - 2.8196) - \Phi(-1.96 - 2.8196) \simeq 1 - \Phi(0.8596) \simeq 0.805$$

- This implies that, in order to achieve a power of 0.8, we need a total of  $4 \times 12 \times 9 = 432$  observations.

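### Risk-adjustment covariates are chosen by p-value on about 108 step-1 patients and the ÖMPQ is kept out of the model, which gives up precision the trial has already collected

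*Protocol*

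**What the plan says.** The Risk Adjustment section sets a selection rule. The screen comes first: "First, using data from step 1 (before any therapists have commenced intervention) univariate analyses will be used to identify possible confounding variables". Eight candidates are named from earlier literature, among them age, sex, severity, onset and employment status. Baseline PSFS is not named as such, and severity is not defined. The second step is "Each patient characteristic found to be significant in the univariate analyses will be included in the models using a backward-deletion process". The section then commits all analysis of the intervention effect to the risk-adjusted PSFS and EQ-5D, and the first hypothesis is worded on risk-adjusted outcomes. The model in the power calculation, and the ANOVA with random intercept under Statistical methods, contain no patient covariates. Adjustment is therefore a separate first stage.

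Psychosocial Screening introduces the ÖMPQ as something additional to risk adjustment. It justifies measuring distress because "such factors are strong predictors of outcome in musculoskeletal conditions", and selects the ÖMPQ for its predictive ability. The use it prescribes is that "any improvements (or lack of improvements) in the other outcome measures need to be cross-referenced with these profiles". The instrument is scored at the start of treatment. The Variables section nevertheless counts patient prognostic barriers among the control variables.

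**The concern.** Three features of the rule are weak. Significance screening in a small subset keeps or drops covariates partly by chance. A covariate can be lost for the whole trial because of one test on a quarter of the patients. The one instrument the protocol itself describes as predictive is not eligible for the model.

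At stake is precision in the primary comparison, and protection against differences in case mix between small therapist-by-period cells. Such differences need not be pure chance: under Randomisation, patients are recruited by their own physiotherapist, who under Blinding knows whether training has taken place. Baseline PSFS and ÖMPQ are already collected on each patient, so using them costs no data.

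**Working it through.** **Inputs from the protocol.** I = 12 physiotherapists, T = 4 steps, N = 9 patients per physiotherapist per step, τ = 1, σ_ε = 2, θ = 1 ("mean changes on the PSFS from usual training to the new training of 1 point"). The test is two-sided at 5% ("based on the usual 95% confidence level"). Appendix E gives U = 24, W = 224, V = 56.

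**Reproducing the stated power.** With s² = σ_ε²/N = 4/9:

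Var = I·s²·(s² + Tτ²) / [(IU − W)s² + (U² + ITU − TW − IV)τ²]

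- Numerator: 12 × 0.4444 × 4.4444 = 23.704
- Denominator: (288 − 224) × 0.4444 + (576 + 1152 − 896 − 672) = 28.444 + 160 = 188.444
- Var = 0.12579, SD = 0.35466, θ/SD = 2.8196, power = Φ(2.8196 − 1.96) ≈ 0.805

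This matches Base case details and Appendix E. No covariate adjustment is credited in it.

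**What the screen can detect.** Step 1 has 12 × 9 = 108 of the 432 patients. By Fisher's z, the chance of passing at p < 0.05 is about Φ(atanh(r)·√105 − 1.96). For r = 0.20 this is Φ(0.2027 × 10.247 − 1.96) = Φ(0.117) = 0.55.

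| True r | Chance of passing |
|---|---|
| 0.10 | 18% |
| 0.15 | 34% |
| 0.20 | 55% |
| 0.30 | 89% |
| 0.40 | 99% |
| 0.50 | about 100% |

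If all eight candidates were null and independent, at least one would pass with probability 1 − 0.95⁸ = 34%.

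**Effect on variance.** R² is not given, so a range was simulated: 1,500 runs per scenario, 432 patients, 12 therapists, τ = 1, patient-level SD 2, true effect 1. The candidates were a baseline measure and six noise variables. Screening and backward deletion both used step 1. Entries are the variance of the estimated effect.

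| r baseline / r ÖMPQ | Both fixed, one stage | Screened, no ÖMPQ | Two-stage adjusted outcome | Excess over fixed |
|---|---|---|---|---|
| 0.2 / 0.2 | 0.1116 | 0.1198 | 0.1225 | 7 to 10% |
| 0.3 / 0.3 | 0.1073 | 0.1211 | 0.1233 | 13 to 15% |
| 0.5 / 0.3 | 0.0835 | 0.0948 | 0.0968 | 14 to 16% |
| 0.5 / 0 | 0.0936 | 0.0937 | 0.0953 | 0 to 2% |

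The third row can be checked on the protocol's formula. Baseline alone (R² = 0.25) gives 0.09559. Baseline plus ÖMPQ (R² = 0.25 + 0.09 = 0.34, s² = 4 × 0.66/9 = 0.2933) gives 3.52 × 4.2933 / (18.773 + 160) = 0.08453. The ratio is 1.13, in line with the simulated 1.14 for the screened route.

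**Effect on power.** Replace σ_ε² by 4(1 − R²) at N = 9:

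- R² = 0.05: s² = 0.4222, Var = 0.1198, power 0.824
- R² = 0.10: s² = 0.4000, Var = 21.12/185.6 = 0.1138, power 0.842

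**The case against.** The best defence is that the protocol does adjust, and that severity is on its list. If severity means baseline PSFS, a reader who compares baseline adjustment with none would infer too much. Assume the SD of 2 refers to change, SDs are equal at baseline and discharge, and the baseline-to-discharge correlation ρ is 0.3 to 0.5. Residual variance then falls to (1 + ρ)/2 = 65 to 75%, and power on the protocol's formula becomes 0.93 to 0.90. The same assumptions imply a correlation between baseline and change of −√((1 − ρ)/2), about −0.59 to −0.50, which passes the screen at n = 108 almost every time. Most of that gain is therefore not lost, and the last simulation row shows it. This part of the defence stands.

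It also stands that predictors with r of 0.15 to 0.20 explain only 2 to 4% of variance each, that a false pick costs little among 432 patients, and that the two-stage step by itself adds only about 2% to variance. Choosing covariates before any therapist is trained prevents tuning the choice to the treatment effect, though a list named in advance has the same merit. The ÖMPQ overlaps with duration, work and function, so its added value could be smaller than assumed.

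A reader might also set Table 1 ("Items previously shown in other studies to be useful for risk adjustment and cost effectiveness are included") against the baseline form and conclude that surgery, exercise history and reimbursement are not collected. The public copy does not support this: part of that form has been removed, and the part shown has a sick pay and benefits item.

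Leaving the covariate list to an analysis plan would be no fault. Here, however, the protocol itself fixes the selection rule and the role of the ÖMPQ.

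**Conclusion.** The point holds at modest size. The rule guarantees no covariate, is unstable for moderate predictors, and leaves the ÖMPQ for cross-referencing only, in conflict with the Variables section. The cost is roughly 7 to 16% in variance if the ÖMPQ is prognostic at r of about 0.2 to 0.3 independently of baseline, and close to nil if it adds nothing. On the protocol's own formula, covariates explaining 5 to 10% of variance are worth about 0.02 to 0.04 in power.

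These figures rest on an R² that the protocol does not give, on 12 therapists with 9 complete patients each, and on backward deletion also using step 1, which is the natural reading but is not stated. They do not show that the trial falls below its 0.80 target: the stated 0.805 takes no credit for covariates, so better adjustment is a gain over the plan.

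**What to change.** Replace the screen and the two-stage outcome with a one-stage mixed model. Use discharge PSFS as the response, with baseline PSFS, ÖMPQ total, age, sex and symptom duration as fixed covariates named now, alongside period, intervention and the random effects. Treat EQ-5D the same way with its own baseline value. Reword Risk Adjustment, Psychosocial Screening and Variables so that they agree on the role of prognostic barriers, and define severity if the term is kept.

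The cost is protocol wording only. Baseline PSFS, the ÖMPQ, sex, date of birth and symptom duration are already collected at the start of treatment, and no extra patients are needed.
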